### **5.4.2 Secondary endpoints**

Overall survival (OS): OS for first-line treatment, from the start of first-line treatment until death, and for surviving patients, until the date of last follow-up.

## **5.5 Statistical analysis plan**

### **5.5.1 Sample size calculation**

For the ICI subgroup, a novel clinical prediction model based on binary logistic regression was to be developed. Referring to the DIREct-On study, which enrolled 72 patients and developed an excellent model with 3 variants (peripheral CD8 T cell levels, ctDNA dynamics and ctDNA adjusted TMB) as input, we also planned 3 variants for the modeling. The prevalence of durable clinical benefit (DCB) from ICI treatments was around 30%-70%. With the criterion of 10 Events Per Variable (10 EPV), the minimal sample size required for the study was 60-100 patients.

For the targeted therapy subgroup, the sample size estimation was basically according to the prevalence of each target, as it was a descriptive study of clonal evolution. We planned to enrolled 100 patients treated with ALK-TKI, 25 patients treated with MET-TKI and 25 patients treated with ROS1-TKI.

### **5.5.2 Grouping method**

For the ICI subgroup, patients will be divided into 2 groups with 6 months PFS as the cutoff, with PFS of durable clinical benefit (DCB) group  $\geq 6$  months and non-durable benefit (NDB)  $< 6$  months, referring to the DIREct-On study.

For the targeted therapy subgroup, further grouping includes: primary resistance group (progressed in 3 months), long term benefits (PFS  $\geq 36$  months), and the rest which

could be further divided into PFS  $\geq$  medium reported PFS or not.

### **5.5.3 Statistical analysis**

The database will be transferred to the statistical analysts for statistical analysis in accordance with the plan requirements. The statistical unit prepared a statistical analysis report to the principal investigator who are obliged to complete the study results.

#### **5.5.3.1 Baseline and demographic characteristics**

Baseline demographic characteristics, baseline clinical characteristics, and mutation profiling will be descriptively analyzed for all enrolled patients. For continuous measures, mean, standard deviation, range and median will be calculated; absolute values, frequencies and percentages were calculated.

#### **5.5.3.2 Primary endpoint analysis**

PFS: The Kaplan-Meier method will be used to describe the 25%, 75%, and median event occurrence times, along with a 95% two-sided confidence interval, and to plot the Kaplan-Meier survival curve up to the time of data cutoff. The COX proportional risk regression model was used for each covariate to test the influence factors related to the prognosis of recurrence in terms of hazard ratios (HR) and their estimated 95% two-sided confidence intervals.

For the ICI subgroup, recapitulation of the DIREct-On model will be tried and binary logistic regression approached will be used to develop novel multimodal models.

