tumor mutation burden (TMB), PD-L1 expression, and circulating tumor DNA (ctDNA) are insufficient to predict therapeutic efficacy from PD-1/PD-L1 inhibitors.

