## 2 Study objectives and study endpoints

| Study objectives                                                                                   | Study endpoints |
|----------------------------------------------------------------------------------------------------|-----------------|
| Primary study objective                                                                     | Primary study   |
| To establish a multimodal model to predict the efficacy of ICI treatments                          | endpoint
PFS |
| Secondary study objective                                                                   | Secondary study |
| To explore mutations associated with hyperprogression and severe toxic side effects in ICI Therapy | endpoint
OS  |
| Exploratory study objective                                                                 |                 |
| To investigate clonal evolution of tumor cells treated with ICI or TKI                             |                 |

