#### **5.5.3.3 Secondary endpoint analysis**

OS: The Kaplan-Meier method will be used to describe the 25%, 75%, and median event occurrence times, along with a 95% two-sided confidence interval, and to plot the Kaplan-Meier survival curve up to the time of data cutoff. The COX proportional risk regression model will be used for each covariate to test the influence factors related to the prognosis of recurrence in terms of hazard ratios (HR) and their estimated 95% two-sided confidence intervals.

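### The aim is worded as predicting ICI efficacy, but an all-ICI cohort with unadjusted per-covariate Cox models and no clinical benchmark can show only association with outcome under ICI

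*Protocol*

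**What the plan says.** **Aim.** Protocol section 2 gives the primary objective as "To establish a multimodal model to predict the efficacy of ICI treatments", and section 3.1 describes the design in the same terms. Section 1.1 motivates the work by saying that imaging, tumour markers, TMB, PD-L1 expression and ctDNA "are insufficient to predict therapeutic efficacy from PD-1/PD-L1 inhibitors". Section 1.2 is narrower: it speaks of predicting DCB. Section 5.5.2 defines DCB as PFS of at least 6 months.

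**Association analysis.** For PFS, section 5.5.3.2 says "The COX proportional risk regression model was used for each covariate to test the influence factors related to the prognosis of recurrence". For OS, section 5.5.3.3 says "The COX proportional risk regression model will be used for each covariate to test the influence factors related to the prognosis of recurrence". Neither names an adjustment set, and neither sentence is limited to ICI patients.

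**Model building.** For the ICI subgroup, section 5.5.3.2 adds that "recapitulation of the DIREct-On model 21 will be tried and binary logistic regression approached will be used to develop novel multimodal models". On the number of inputs, section 5.5.1 says "we also planned 3 variants for the modeling". The only variables named there are those of the earlier study: "3 variants (peripheral CD8 T cell levels, ctDNA dynamics and ctDNA adjusted TMB) as input".

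**Patients and data.** The modelling cohort is EGFR/ALK-negative and all on first-line ICI (sections 4.1 and 5.1). The other patients carry ALK, ROS1 or MET alterations, receive a TKI, are studied descriptively and have ctDNA analysis only (sections 3.1 and 3.3). ECOG PS is in the test schedule (section 5.3). Stage and histology have to be known for eligibility (section 4.1).

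**The concern.** There are two gaps between the aim and the analysis.

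First, a claim about ICI efficacy, read strictly, is a claim that the marker changes what ICI achieves. Testing that needs similar patients not given ICI and a marker-by-treatment interaction. The protocol has no such patients. The TKI cohort cannot stand in: it is a different molecular population on a different treatment, and it lacks the PBMC-RNA measurements.

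Second, even for the narrower question of outcome under ICI, the stated Cox analysis takes covariates as they come, without adjustment. The logistic step is multi-input, but fitting blood markers jointly adjusts them for each other and not for fitness or tumour burden. If blood markers follow performance status or disease extent, they are credited with that information. The report could then present a multimodal ICI-efficacy model whose content the clinician largely had at baseline, and no stated analysis would show it.

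**Working it through.** **1. The plan's own figure.** Section 5.5.1 uses 10 events per variable and 3 inputs, with this DCB range: "The prevalence of durable clinical benefit (DCB) from ICI treatments was around 30%-70"%. Counting the smaller outcome class as events, N = 10 × 3 / min(p, 1−p):
- p = 0.5: 30/0.5 = 60
- p = 0.3 or 0.7: 30/0.3 = 100

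This reproduces the stated 60-100. The ICI allocation agrees: 250 − (100 + 25 + 25) = 100. The sizes used below are therefore N = 60 and N = 100.

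**2. Can the design isolate an ICI effect?** In the modelling cohort treatment is constant, so a marker-by-treatment term cannot be estimated at any N. This follows from eligibility and needs no simulation.

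**3. How often does a purely prognostic marker look informative? DCB, logistic.** All inputs except N are assumptions. A prognostic score z is standard normal; the marker is x = r·z + √(1−r²)·e and has no effect of its own; logit P(DCB) = ln(OR)·z, so DCB is about 50%. OR is 1.8 or 2.5 per SD, with 2,000 trials per setting and a likelihood-ratio test at 5%.

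| N | r = 0.3 | r = 0.5 | r = 0.7 |
|---|---|---|---|
| 100, x alone | 13-21% | 27-50% | 50-79% |
| 60, x alone | 11-16% | 19-35% | 33-59% |

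Testing x with z already in the model gives about 5% in every setting. A rerun with a different random seed agreed to within about two percentage points.

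**4. The same question for PFS, one-covariate Cox.** Assumptions: median PFS 7 months, prognostic HR 1.5 or 2.0 per SD, uniform censoring at 6-30 months, two-sided 5%, 600 trials per setting.

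| N | r = 0.3 | r = 0.5 | r = 0.7 |
|---|---|---|---|
| 100, x alone | 18-30% | 40-70% | 63-97% |
| 60, x alone | 11-23% | 24-48% | 42-80% |

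Adjusted for z, the share is 4-6% throughout.

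**5. Room for a clinical comparator at N = 100.**
- Three markers plus one clinical score is 4 parameters. With 30% DCB, 30/4 = 7.5 events per parameter; with 50%, 50/4 = 12.5.
- Entered separately, ECOG 0/1/2 (2 terms), stage (1) and histology (1) make 4 terms, or 7 parameters with the markers: 30/7 = 4.3 and 50/7 = 7.1.
- Under the 10-EPV rule, 4 parameters need 40/0.5 = 80 to 40/0.3 ≈ 134 patients, against about 100 available.

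**The case against.** **The Cox sentence is about prognosis.** A prognostic factor that is significant there is a correct result. This stands. A reader might infer that the plan tests covariates one at a time and passes any significant one as an ICI-efficacy predictor. The protocol does not support that: it states no null hypothesis, significance level or selection rule, and the primary aim is served by the multi-input logistic models and the DIREct-On recapitulation.

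**The three new inputs are not named.** The variables in parentheses belong to the earlier study, so a clinical variable is not excluded. This also stands. A reader might take the model to be fixed as three blood markers; it is not. What remains is that no stated analysis sets the final model against a clinical baseline, whatever its inputs.

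**A model for outcome under one treatment needs no comparator and may use prognostic information.** Correct, and sections 1.2 and 5.5.2 largely describe such a model. The wider wording is in sections 2 and 3.1.

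**Adjustment sets may sit in a separate SAP.** Possible. But section 5.5 carries that title and fixes the outcome split, the model type and the number of inputs, and the aim is protocol content in any case.

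**The benchmark is not the one section 1.1 raises.** ECOG PS, stage and histology are not among the tools listed there as insufficient. The comparison below would not test improvement on PD-L1 or TMB.

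**The simulation is favourable to adjustment.** It tests a single marker and adjusts for an error-free score. Both limits stand.

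**Conclusion.** The point holds in a limited form. As designed, the study can show association with outcome under first-line ICI, and sections 2 and 3.1 claim more than that. This part rests on the eligibility criteria alone. In addition, the stated per-covariate Cox analysis is unadjusted and no clinical benchmark is stated, so a marker that tracks baseline prognosis can appear informative.

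The size depends on assumed values that the protocol does not give. For correlations of 0.3-0.7 and a prognostic OR of 1.8-2.5 per SD, about 13-79% of unadjusted 5% tests at N = 100 are significant, against about 5% after adjustment for a perfectly measured score. With ECOG PS, stage and histology as imperfect proxies, some confounding would remain. These percentages describe one marker tested alone; they are not an error rate for the planned multi-input model. Nor should adjustment be read as making a marker ICI-specific: it removes measured prognosis only, which is why the wording has to change as well. The change is worth making, but it does not undermine the study.

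**What to change.** 1. **Sections 2 and 3.1.** Word the aim and the conclusion as predicting DCB (PFS of at least 6 months) in patients treated with first-line ICI, in line with sections 1.2 and 5.5.2.
2. **Sections 5.5.3.2 and 5.5.3.3.** For the ICI subgroup, report per-marker hazard ratios adjusted for the recorded ECOG PS, stage and histology.
3. **Section 5.5.3.2.** Compare the final DCB model with a reference model of those clinical variables: a likelihood-ratio test of the reference against the reference plus the model's inputs, and the change in AUC with its 95% CI. Enter the clinical variables as one prespecified or penalised score.

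The final model keeps its three planned inputs, so its 10-EPV basis is unchanged. No patients, samples or visits are added.

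**Cost.** The comparison model has about 7.5-12.5 events per parameter at N = 100 with 30-50% DCB, and only about 4-7 if the clinical variables are estimated as separate terms in the same data. The documents contain no ready-made score, so one has to be specified in advance or the terms penalised. Report the comparison as a secondary benchmark and expect wide intervals. Marker effects may look smaller than in the unadjusted analysis.

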## 1.2 Study rationale

Recently, a research team from Stanford University established the DIREct-On model, which combines blood TMB (bTMB), changes in ctDNA, and peripheral blood CD8+ T cells to predict whether patients will benefit from long-term treatment with PD-1/PD-L1 inhibitors. In the retrospective study, DIREct-On model could predict patients who would achieve durable clinical benefit (DCB, over 6 months) with high accuracy. Inspired by this study, we designed this prospective multicenter clinical trial to explore multimodal models that were more feasible in the clinical routine for predicting DCB of ICI treatments in non-EGFR/ALK NSCLC patients.

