### **3.3 Duration and sample size**

The original plan was to commence in July 2020 and conclude participant enrollment by June 2023. (However, due to the COVID-19 pandemic, the enrollment is still ongoing)

The planned enrollment for this study was 250 participants from multiple centers, including *EGFR/ALK* negative NSCLC patients who received first-line ICI treatment, and NSCLC patients with *ROS1* fusion, *ALK* fusion or *MET* exon 14 skipping mutation treated with corresponding TKI. The sample size estimation was listed as the following: For the ICI subgroup, a novel clinical prediction model based on binary logistic regression was to be developed. Referring to the DIREct-On study, which enrolled 72 patients and developed an excellent model with 3 variants (peripheral CD8 T cell levels, ctDNA dynamics and ctDNA adjusted TMB) as input, we also planned 3 variants for the modeling. The prevalence of durable clinical benefit (DCB) from ICI treatments was around 30%-70%. With the criterion of 10 Events Per Variable (10 EPV), the minimal sample size required for the study was 60-100 patients.

For the targeted therapy subgroup, the sample size estimation was basically according to the prevalence of each target, as it was a descriptive study of clonal evolution. We planned to enrolled 100 patients treated with ALK-TKI, 25 patients treated with MET-TKI and 25 patients treated with ROS1-TKI.

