### **5.4.1 Primary endpoint**

Progress Free survival (PFS): PFS for stage IIIB-IV NSCLC who received first-line systemic therapy was defined from the start of first-line systemic therapy to disease progression or death. Disease progression was defined according to RECIST 1.1 criteria. The date on that patients receive their last imaging evaluation while alive and progress-free is used as the cutoff.

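### The multimodal model is fitted by logistic regression on a 6-month split of a censored PFS endpoint, which literally labels patients lost progression-free before 6 months as non-durable benefit and gives up information on predictor effects

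*Protocol*

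**What the plan says.** Protocol section 2 pairs the primary objective, "To establish a multimodal model to predict the efficacy of ICI treatments", with PFS as the primary endpoint. Section 5.4.1 defines PFS as a time: it "was defined from the start of first-line systemic therapy to disease progression or death". For patients without an event it adds: "The date on that patients receive their last imaging evaluation while alive and progress-free is used as the cutoff". The natural reading is censoring at the last progression-free scan.

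The model is specified differently. Section 5.5.2 says that for the ICI subgroup "patients will be divided into 2 groups with 6 months PFS as the cutoff", with DCB at 6 months or more and NDB below 6 months. Section 3.3, repeated in 5.5.1, says that "a novel clinical prediction model based on binary logistic regression was to be developed", with three predictors, and section 5.5.3.2 confirms that "binary logistic regression approached will be used to develop novel multimodal models".

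Two other statements matter. Section 1.2 gives the aim as multimodal models "for predicting DCB of ICI treatments in non-EGFR/ALK NSCLC patients". Section 5.5.3.2 also plans Kaplan-Meier curves for PFS and a regression on PFS times: "The COX proportional risk regression model was used for each covariate to test the influence factors".

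**The concern.** The endpoint is a censored time, but the model for the primary objective sees only which side of 6 months the time falls. Two consequences follow.

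First, labelling. A patient last scanned progression-free at month 3 and then lost has an observed PFS of 3 months. Under section 5.5.2 that is below 6 months and therefore NDB, although nobody knows whether the patient would have reached 6 months. A model trained on such labels learns loss to follow-up as treatment failure, and its predicted DCB is too low.

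Second, efficiency. Progression at 1 month and at 5.9 months count alike, as do 6.1 and 30 months. That costs precision on the predictor effects in a cohort with no spare patients. The Cox analysis in section 5.5.3.2 does not repair this: as written it tests covariates singly, and logistic regression is the only method named for the multimodal model.

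**Working it through.** **Inputs from the protocol.** Three predictors, 10 events per variable (EPV), DCB prevalence 30% to 70%, and 60 to 100 ICI patients (sections 3.3 and 5.5.1). Total enrolment is 250, with 100 + 25 + 25 = 150 on TKIs (section 3.3). The study ends when over 70% have progressed (section 3.2).

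**Assumptions not in the protocol.** Exponential PFS, proportional hazards, the effect sizes, the early-loss rates, and the study-wide 70% taken as the PFS event fraction in the ICI cohort.

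**1. The plan's own figure.** 3 × 10 = 30 patients are needed in the smaller outcome class, so N = 30/min(p, 1−p).
- p = 0.5: 30/0.5 = 60.
- p = 0.3 or 0.7: 30/0.3 = 100.

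The stated 60 to 100 is reproduced. The ICI cohort is 250 − 150 = 100 (derived), exactly the upper limit, so there is no margin at the ends of the prevalence range.

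**2. Literal labelling.** Let S be the true probability of PFS of at least 6 months and d the probability of loss before 6 months, independent of PFS. The share labelled DCB is S(1−d), a fall of d × S. A logistic model with an intercept reproduces that share on average.
- S = 0.3, d = 10%: 0.10 × 0.30 = 3 points.
- S = 0.7, d = 20%: 0.20 × 0.70 = 14 points.

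Simulation with 100 patients and three predictors gave about 4 to 14 points for 10% to 20% early loss, in line with this.

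**3. Excluding these patients instead.** With a fraction c unclassifiable, taken as equal in both classes, and 30 in the smaller class before exclusion:
- c = 5%: 30 × 0.95 = 28.5; EPV 28.5/3 = 9.5; N needed 100/0.95, rounded up to 106.
- c = 20%: 30 × 0.80 = 24; EPV 24/3 = 8.0; N needed 100/0.80 = 125.

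At 50% DCB the required N rises from 60 to between 64 and 75, which 100 patients cover. The shortfall is therefore at the ends of the stated range.

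**4. Information lost by the split.** For exponential PFS near the null, the split carries S(ln S)²/(1−S) per patient on the log hazard ratio. Cox carries the event fraction.

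| S | Split | Retained at 70% events | Lost at 70% events | Lost if all have events |
|---|---|---|---|---|
| 0.3 | 0.621 | 0.621/0.70 = 0.89 | 11% | 38% |
| 0.5 | 0.480 | 0.480/0.70 = 0.69 | 31% | 52% |
| 0.7 | 0.297 | 0.297/0.70 = 0.42 | 58% | 70% |

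The 11% is a boundary case: at S = 0.3, 70% already have an event by month 6, so a 70% event fraction means that no later event is observed.

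Finite-sample simulations, each with 100 patients, gave:
- Three predictors, no early loss: logistic has 0.42 to 0.61 of Cox's efficiency, a loss of 39% to 58%.
- One predictor (log HR 0.4 per SD), 10% early loss with those patients excluded, 66% to 73% events: 0.64, 0.60 and 0.44 retained at S = 0.3, 0.5 and 0.7. Power for logistic against Cox is 0.81 against 0.90, 0.72 against 0.86, and 0.54 against 0.86.

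**5. Effect on prediction.** In simulation, Cox gained about 0.005 to 0.01 in out-of-sample AUC for 6-month DCB without early loss, and about 0.01 to 0.02 with it.

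**The case against.** The best defence is that 6-month DCB is the declared target. Section 1.2 says so, section 5.5.2 adopts the DIREct-On definition, and the sample size is built on it. Treating 6.1 and 30 months alike is what that target means. This stands: the split is deliberate and should remain the prediction target. It does not oblige the model to be fitted on the split, because a Cox model also yields a 6-month PFS probability.

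The second defence is that power for one coefficient is the wrong measure for a prediction study, and that the AUC gain is small even under exact proportional hazards, which favours Cox. This also stands, and it limits the efficiency argument. It does not answer the labelling problem, which affects the level of the predicted probabilities.

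Third, handling of early censoring is often left to a separate SAP. But the point is not that a rule is absent. The two stated rules, taken together, assign the wrong label, and they do so within sections 5.4 and 5.5, the latter itself titled a statistical analysis plan.

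A reader might go further in three ways that the document does not support:
- **That the model cannot use censored patients.** Anyone censored at or after 6 months is validly DCB. In the one-predictor simulation, 75% to 79% of censored patients were usable.
- **That half the information is lost as a fixed fact.** The share depends on DCB prevalence and event fraction.
- **That Cox has 23 events per variable (70/3) against 10.** The 10 is the worst prevalence limit. Across 30% to 70% DCB the smaller class is 30 to 50, or 10 to 17 per predictor.

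**Conclusion.** The point holds in a limited form. The protocol's primary endpoint is censored PFS, its multimodal model is logistic on a 6-month split, and the two rules combined misclassify patients lost progression-free before 6 months.

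The misclassification is the stronger part: about 4 to 14 points off predicted DCB if 10% to 20% are lost early, or EPV of 9.5 to 8.0 at 30% or 70% DCB if 5% to 20% are excluded. Both loss ranges are assumed; the protocol gives no loss rate.

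The efficiency loss is roughly 40% to 60% of the information on predictor effects in simulation, and 11% to 58% by formula at exactly 70% events. It depends on DCB prevalence, event fraction and proportional hazards, and it costs only about 0.005 to 0.02 in 6-month AUC.

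It would be wrong to infer that the logistic model is invalid or that PFS times go unused: Kaplan-Meier and per-covariate Cox analyses of PFS are planned. The change is worth making because it is cheap and uses data already collected.

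**What to change.** In section 5.5.3.2:
- State that 6-month DCB remains the prediction target for the ICI cohort.
- Fit the three-predictor multimodal model by Cox regression on PFS, penalised if needed.
- Report predicted 6-month PFS, with time-dependent AUC and calibration at 6 months.
- Check proportional hazards.
- Retain the logistic DCB/NDB model for comparability with DIREct-On.

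In section 5.5.2, state that a patient censored progression-free before 6 months is not NDB, and say how the logistic model handles such patients, for example by inverse-probability-of-censoring weights. Simple exclusion is less good: patients who progress before they would have been lost stay in as NDB, so some downward bias remains.

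In section 2, name 6-month DCB beside PFS as what the model predicts.

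The cost is wording, modest programming and reliance on proportional hazards. If that assumption fails, Cox could predict 6-month status worse than the logistic model, so both should be reported. No new data are needed.
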